#### Drop-out criteria

The drop-out criteria are:
Consent withdrawalSafety concernsSelection criteria violations

Participants may exit the study for personal reason at any time. In this case, no new data will be collected since the date of withdrawal. Data collected prior to the date of withdrawal may still be used. In case of serious adverse reaction related to the usage of the experimental bougie, the investigator must notify the sponsor without delay. The participation will be discontinued but the participant will continue to be monitored for the study.

### Who will take informed consent? {26a}

Patients who are candidates for LSG at participating hospitals are invited to participate in the trial. Surgeons determine participant eligibility, discuss the trial and seek informed consent during routine bariatric preoperative assessments. All surgeons involved in obtaining consent and enrolling participants have received specific training in the trial and the requirements of Good Clinical Practice (GCP). They do not necessarily need to be investigators or research staff.

### Additional consent provisions for collection and use of participant data and biological specimens {26b}

Not applicable.

## Interventions

### Explanation for the choice of comparators {6b}

Usage of calibration bougie during sleeve gastrectomy has become an international standard [6], yet no recommendation regarding the bougie diametre has been proposed. Most teams use a bougie diametre of less than 40-Fr [3], mainly 36-Fr [4]. Meta-analysis and systematic review of observational studies have associated the use of a bougie diametre larger than or equal to 40-Fr with a decrease in the rate of leak [3, 11]. However, as with all observational studies, these findings may be affected by selection bias and residual confounding, making causal inferences problematic. No prospective randomized study has investigated the impact of the bougie diametre on the rate of postoperative gastric leak. Increasing the bougie diametre would not affect the surgical procedure, and no failure of introduction of a larger bougie has ever been reported [3]. Most teams preferring a large calibration bougie diametre use a 48-Fr bougie [6]. Hence, the diametre of the bougie in the experimental group was decided to be 48-Fr.

### Intervention description {11a}

Participants will be randomized to one of the two blinded bougie diametre groups:
Experimental group: LSG calibrated on a 48-Fr (16 mm) bougieorControl group: LSG calibrated on a 34-Fr (11.3 mm), 36-Fr (12 mm) or 38-Fr (12.7 mm) bougie according to the centre standard care

After randomization, the anaesthesiologist will collect the corresponding blister containing the calibration bougie. During LSG, the calibration bougie is inserted through the mouth of the patient and placed in the stomach by the anaesthesiologist after gastric dissection. The surgeon uses the bougie to calibrate the remnant stomach during gastric section and stapling. The bougie is thereafter removed during the surgery by the anaesthesiologist. After removal, the bougie will be discarded according to routine practice in each centre. The use of both bougies is the same and instructions will be given to all anaesthesia departments.

Participants allocated in the experimental group will be assigned an individual blister containing the 48-Fr calibration bougie labelled with a unique study code. Experimental bougie is MID-TUBE orogastric calibration tube by Médical Innovation Développement S.A.S (ref. MID131). This is a CE-marked class IIa medical single-use device used in the field of gastroenterology. The device is 791 mm long, in medical silicon rubber, and contains no latex. The experimental bougie is provided by the sponsor to each centre’s pharmacy. Participants allocated in the control group will be assigned a standard care bougie (34-Fr, 36-Fr or 38-Fr) used in accordance with the manufacturer’s instructions. All standard care bougies are single-use devices, used in the indication of their CE marking, which allows the devices to be covered by the national insurance funds. Standard care bougies will not be provided by the sponsor, but they will be supplied by each centre’s pharmacy according to standard care and reimbursed by the French health social system. Experimental 48-Fr bougie and standard care 38-Fr bougie are presented in Fig. 2.

**Fig. 2 Fig2:**
[figure not shown]
Experimental 48-Fr bougie and standard care 38-Fr bougie

### Criteria for discontinuing or modifying allocated interventions {11b}

Intervention may be discontinued by the anesthesiologist at any time if the placement of the bougie is considered inadequate. In this case, the patient remains included in the study but will be treated according to the standard care procedure in each centre. The patient will be analysed in the experimental group according to the “intention-to-treat analysis”.

### Strategies to improve adherence to interventions {11c}

The intervention will be implemented entirely by local teams; thus, adherence to the intervention will be improved by three different methods. First, a preliminary face-to-face workshop will be held in each site, gathering site investigators and research staff to present the project in details, to tailor local resources including checklists and trial alert notices in medical records. Recommendations will be given during the preliminary workshop to standardize the surgical procedure, allowing decreasing the variability between centres. The standardized protocol is used as common practice in the coordinating investigator department, highly experimented in laparoscopic sleeve gastrectomy [12]. Second, a local project liaison will be the direct link between the local investigators and the study team, participating in the implementation of the intervention in each centre. The local project liaison will carry out regular follow-up visits in each centre to verify that the study is carried out in accordance with the current version of the protocol and all statutory and regulatory requirements. Finally, the study team will form a steering committee providing technical expertise and mentorship on project management.

### Relevant concomitant care permitted or prohibited during the trial {11d}

All participants receive usual postoperative management as per the local standard of care. This includes perioperative anaesthesia, surgical care, routine prophylactic measures, postoperative diet and management of complications. Systematic morphological imaging is not mandatory.

### Provisions for post-trial care {30}

Following the intervention, participants are followed up until 24 months after LSG. All postoperative care is provided by the centre where the LSG is performed as per routine practice. The sponsor will provide full compensation for any damages caused by the study to the study participants and their beneficiaries, unless the sponsor can prove that the harm is not the fault of the sponsor or any agent.

### Outcomes {12}

#### Primary outcome measure

The primary outcome is the occurrence of postoperative gastric leak. After LSG, gastric leak is known to occur within the first postoperative month [11]. Gastric leak is consistently a symptomatic complication, as no leak is assumed to stay unnoticed. To date, there is no consensus on the method for the diagnosis of gastric leak. Some teams use systematic morphological examination, and others prefer to rely on clinical and biological examination and proceed in case of suspicion of gastric leak either to immediate reintervention or to morphological investigation. No systematic examination for early detection of gastric leak has been proven to be reliable. In this study, diagnosis of postoperative gastric leak during the first month following the procedure must be fulfilled with either (1) morphologic examination (with contrast ingestion) such as abdominal CT scan or gastrointestinal swallow studies showing extravasation of the contrast material or abnormal perigastric pneumoperitoneum; (2) evidence of staple-line disruption by exit of blue dye during exploratory surgical reintervention or through the drainage during postoperative course; or (3) evidence of staple-line disruption by extravasation of contrast opacification during endoscopy. The method for the diagnosis of gastric leak does not depend on bougie diametre. The occurrence of postoperative gastric leak is notified by the surgeon during the first 3 months following the procedure.

#### Secondary outcome measures

Secondary outcomes are the following:
Global postoperative morbidity, defined as any complication occurring 90 days following the procedure; the severity of postoperative morbidity will be assessed according to the Dindo-Clavien classification of surgical complications [13] (Table 1).Short- and mid-term weight lossShort- and mid-term quality of life

**Table 1 Tab1:** The Clavien-Dindo classification of surgical complications

Grades	Definition
Grade I	Any deviation from the normal postoperative course without the need for pharmacological treatment or surgical, endoscopic and radiological interventions Allowed therapeutic regimens are drugs as antiemetics, antipyretics, analgetics, diuretics and electrolytes and physiotherapy. This grade also includes wound infections opened at the bedside.
Grade II	Requiring pharmacological treatment with drugs other than such allowed for grade I complications Blood transfusions and total parenteral nutrition are also included.
Grade III	Requiring surgical, endoscopic or radiological intervention
Grade IIIa	Intervention not under general anaesthesia
Grade IIIb	Intervention under general anaesthesia
Grade IV	Life-threatening complication (including CNS complications)* requiring IC/ICU management
Grade IVa	Single organ dysfunction (including dialysis)
Grade IVb	Multiorgan dysfunction
Grade V	Death of a patient

*Brain haemorrhage, ischemic stroke, subarrachnoidal bleeding, but excluding transient ischemic attacks (TIA); *IC* intermediate care, *ICU* intensive care unit

In order to determine weight loss evolution, the initial weight will be measured and recorded by the surgeon the day before the procedure. Assessment of short-term weight loss will be performed at 3 and 6 months after the procedure, and assessment of mid-term weight loss will be performed at 1 and 2 years after the procedure by the surgeon using the percentage of excess weight loss and percentage of total weight loss. Percentage excess weight loss (%EWL) is calculated using the formula: %EWL=weight loss (kg)/excess weight (kg). Excess weight is based on the patient’s ideal weight with a BMI of 25 kg/m^2^. Percentage total weight loss (%TWL) is calculated using the formula: %TWL=weight loss (kg)/initial weight (kg).

Quality of life related to health will be assessed at 3 months, 6 months, 1 year and 2 years after the procedure with the French validated version [14] of the GIQLI (Gastrointestinal Quality of Life Index) questionnaire [15] (Additional file 2).

### Participant timeline {13}

As recommended by French Health Authorities, all patient candidates for bariatric surgery take part in a preoperative follow-up of at least 6 months before undergoing bariatric surgery [16]. During this preoperative course, patients will receive an explanation on the study protocol and will be given an information form. The enrolment phase takes place between 2 months and no later than 1 day before surgery. Participants are followed up in the trial from randomization until 24 months after LSG. Follow-up visits are scheduled as standard care after bariatric surgery. Data collection occurs at baseline and at follow-up visits at 3 months ± 1 month, 6 months ± 1 month, 1 year ± 3 months and 2 years ± 3 months after surgery. The participant timeline is presented in Table 2.

**Table 2 Tab2:** Trial schedule of enrolment, intervention and assessments, as recommended by Standard Protocol Items: Recommendations for Interventional Trials (SPIRIT). *M* months, *D* day, *LSG* laparoscopic sleeve gastrectomy, *GIQLI* Gastrointestinal Quality of Life Index

Study period						
	Enrolment	Allocation	Follow-up			
Timepoint	M-2 to D-1	D0	M3	M6	M12	M24
Enrolment						
Eligibility screen	X					
Informed consent	X					
Baseline characteristics	X					
Allocation		X				
Interventions						
LSG with experimental bougie		X				
LSG with standard care bougie		X				
Assessments						
Postoperative gastric leak			X			
Global morbidity			X			
Weight	X		X	X	X	X
GIQLI questionnaire			X	X	X	X

### Sample size {14}

The sample size for the trial (1658 participants) is based on a comparison between two independent groups of the proportions of participants experiencing the primary outcome measure of postoperative gastric leak. We made the hypothesis of a difference of postoperative fistula rates of 3% with a standard care calibration bougie and 1% with a 48-Fr calibration bougie. Considering a bilateral alpha risk of 5% and a power of 80%, we would need to include 1576 patients (788 in each group). A 5% rate of participants lost to follow-up is estimated; therefore, 1658 patients will be included (829 in each group).

### Recruitment {15}

BOUST is a national multicentre research project conducted in 17 centres, each centre performing more than 100 LSG per year. Considering a total number of subjects to enrol of 1658 and an inclusion period of 24 months, the number of subjects to enrol by centre by month is 4 to 5.

Strategies have been implemented to achieve optimal participant enrolment. The trial was designed as a pragmatic protocol with large eligibility criteria. Recruitment of participants is achieved by the surgeon who supervises the preoperative assessments prior to LSG, performs the surgical procedure and fulfils follow-up. An Internet-based secure platform is used for simple and rapid enrolment, randomization and data collection. Trial processes are aligned to usual clinical care after bariatric surgery. Telephone support is provided to local investigators with the ability to access assistance for enrolment and randomization from an investigator of the coordinating centre.

## Assignment of interventions: allocation

### Sequence generation {16a}

Participants are randomized in a 1:1 ratio to either the experimental group (participants will undergo LSG calibrated on a 48-Fr bougie) or the control group (participants will undergo LSG calibrated on a standard care bougie). In order to reduce the imbalance between participants in each group, stratification will be carried out regarding known risk factors for postoperative gastric leak: gender and super-obesity (defined as BMI > 50 kg/m^2^). In each centre, the control group matches with the standard care procedure and the experimental group an identical procedure except for the usage of a 48-Fr bougie. Thereby, stratification will also be carried out regarding centres to reduce the imbalance between participants in each group. The block size would not be known by the investigator as the sample size is sufficient to ensure a correct repartition between the different strata. A potential imbalance at the end of randomization will be taken into account in the statistical analysis. No stratification regarding the modalities of the laparoscopic approach (conventional or single-port laparoscopy) has been defined as the modalities of the laparoscopic approach are consistent with the centre.

### Concealment mechanism {16b}

Randomization is performed via a secure server dedicated to electronic management of clinical research (CleanWEB®, Telemedicine Technologies, Boulogne-Billancourt, France). The code for generating group allocation was developed by a statistician independent to the project.

### Implementation {16c}

Participants are enrolled by local investigators between 2 months and no later than 1 day before surgery. Inclusion is completed using an Internet-based platform. Randomization is performed on the day of surgery by local investigators via a secure server. After allocation, the assigned calibration bougie is used during LSG.

## Assignment of interventions: blinding

### Who will be blinded {17a}

This is a single-blind randomized clinical trial, as study participants are blinded. After randomization, the anaesthesiologist will collect the corresponding blister containing the calibration bougie and will insert the bougie through the mouth in the stomach before the gastric section. As much as possible, the anaesthesiologist will try to prevent the surgeon from identifying which bougie is used. However, since the aspect and conditioning of experimental bougies are different than those of standard care bougies, it is difficult to ensure the blinding of the surgeon before, during and after the surgical procedure. Nonetheless, the blinding will be maintained for the participant and biostatisticians throughout the study and analyses.

### Procedure for unblinding if needed {17b}

Procedures for unblinding are not necessary since the use of standard care or 48-Fr bougie does not change intraoperative or postoperative management.

## Data collection and management

### Plans for assessment and collection of outcomes {18a}

Data is collected using an electronic case report form (CRF) via CleanWEB®. Trial processes are embedded within the CRF to improve trial efficiency. Clinical data are collected by study staff from the participant’s medical record. Information on health-related quality of life is collected by participant completion of the GIQLI questionnaire.

### Plans to promote participant retention and complete follow-up {18b}

As routine care after bariatric surgery, patients accept to take part in a multidisciplinary follow-up programme. Follow-up visits are timed to coincide with routine outpatient clinic appointments undertaken as part of standard care after LSG. The study staff collects the data required for each visit from medical records. In case of discontinuation or deviation from intervention protocol, the CRF will list the various reasons why the participant has discontinued the study. If a participant discontinues the study, this will in no way affect their usual care for his condition. If a participant exits the study prematurely or withdraws consent, any data collected prior to the date of premature exit may still be used. If a participant is lost to follow-up, the investigator must make every effort to reconnect with the participant, at least to determine whether the participant is alive or dead. Since there is a low chance of not evaluable subject, if a subject is not evaluable, his identification number will not be reallocated and he will not be replaced.

### Data management {19}

All data required for the protocol are collected using a CRF via CleanWEB® at each time point of the follow-up. Non-identifying data will be entered by a clinical research technician. Sources of collected data are medical records and appointment records. Source documents will be kept by each centre in case of medical reports. Documents specific to the trial will be archived by the investigator and the sponsor for 15 years following the end of the study in accordance with national guidelines. Data entry will be carried out on electronic media via a Web browser. Secured login and password will be attributed by a data manager. The CRF’s programming will limit invalid data as much as possible by restricting the possible values to type during the online completion of CRF. Each missing data item must be coded.

### Confidentiality {27}

Any information that may identify a participant will be excluded from the data presented in the public arena. All study-related information is stored securely in each study site. CRF are identified by a coded identification only and stored on secure servers. The electronic data collected for the study is used in accordance with French (“Informatique et Libertés” law governing data protection) and European (General Data Protection Regulation) regulations. This research is governed by the CNIL (French Data Protection Agency). Study staff, as well as the investigators themselves, are bound by professional secrecy (in accordance with the conditions set out in Articles 226-13 and 226-14 of the Code Pénal).

### Plans for collection, laboratory evaluation and storage of biological specimens for genetic or molecular analysis in this trial/future use {33}

No biological specimens are collected in this study.

## Statistical methods

### Statistical methods for primary and secondary outcomes {20a}

Analyses will be by intention to treat. The impact of the bougie calibration diametre, 48-Fr versus 34- to 38-Fr, on the primary outcome of postoperative gastric leak rate during the first postoperative month will be analysed using a logistic regression model, with group, and stratification factors (centre, gender, super-obesity). The primary comparison will be a two-sided test at the 5% significance level. The impact of the bougie calibration diametre on secondary outcomes will be analysed using statistical methods appropriate for the type of outcome. Logistic regression will be used in a multivariate model to identify factors independently associated with morbidity. The normal distribution will be tested using the Shapiro-Wilk test. Should this be significant at the 5% level, a non-parametric approach (Mann-Whitney test) or variable transformation will be used.

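### A Shapiro-Wilk pre-test picks the analysis of weight loss and quality of life, with an open choice of fallback; one prespecified adjusted linear model would serve better

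*Protocol article*

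**What the plan says.** Section 20a (statistical methods for primary and secondary outcomes) says that secondary outcomes will be "analysed using statistical methods appropriate for the type of outcome". It then fixes a rule: "The normal distribution will be tested using the Shapiro-Wilk test", followed by "Should this be significant at the 5% level, a non-parametric approach (Mann-Whitney test) or variable transformation will be used". The variables are not named. Among the listed outcomes only %TWL, %EWL and the GIQLI score are continuous, so the rule must be meant for them.

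The primary outcome is treated differently, "using a logistic regression model, with group, and stratification factors (centre, gender, super-obesity"). Under sequence generation (16a), "stratification will also be carried out regarding centres to reduce the imbalance between participants in each group", in addition to gender and super-obesity. The same section adds: "A potential imbalance at the end of randomization will be taken into account in the statistical analysis".

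The secondary outcome section says that "the initial weight will be measured and recorded by the surgeon the day before the procedure", so baseline weight is available. GIQLI is scheduled only after surgery, at months 3, 6, 12 and 24; Table 2 shows no baseline score. The Discussion calls mid-term weight loss a key secondary outcome, and the Abstract says the trial should show whether leaks fall without harm to mid-term weight loss and quality of life.

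**The concern.** The rule has three weaknesses.

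- **It responds to sample size rather than need.** A normality test gains power as N grows, while a comparison of means becomes less dependent on normality. In a trial of this size the test can reject for departures that do no damage.
- **It does not determine an analysis.** After a rejection the analyst may use ranks or a transformation. No criterion separates the two and no transformation is named. With three measures at four visits there are up to 3 × 4 = 12 gates if each is tested separately. The same outcome could be compared by means at one visit and by ranks at the next.
- **The fallbacks suit the aim poorly.** A statement that weight loss is not impaired needs a between-arm difference with a confidence interval narrow enough to exclude a relevant loss. The ordinary Mann-Whitney test yields no adjusted mean difference and cannot carry centre, gender, super-obesity or baseline weight. A transformed outcome can be adjusted, but its estimate is no longer in percentage points or GIQLI points.

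At stake are the precision and readability of the secondary results.

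**Working it through.** **1. The size at which the gate operates.** Inputs from the sample size section: 3% against 1%, two-sided 5%, 80% power, 1:1. With pooled variance under the null,

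n per arm = [1.96·√(2·0.02·0.98) + 0.8416·√(0.03·0.97 + 0.01·0.99)]² / 0.02² = (0.3881 + 0.1662)² / 0.0004 ≈ 769.

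The protocol's 788 per arm (1576) is within 3% of this and gives 81.0% power. Loss to follow-up: 1576/0.95 = 1658.9, stated as 1658. So about 788 per arm is the right scale. The protocol does not say whether the normality test is run per arm (N=788) or on both arms together (N=1576), so both are shown. N=100 and N=600 are added for contrast and for attrition.

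**2. How often the gate fires.** Share of simulated samples (500 per cell) with Shapiro-Wilk p < 0.05. The protocol gives no SD or skewness for these outcomes, so the shapes are assumptions.

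| Assumed shape | N=100 | N=600 | N=788 | N=1576 |
|---|---|---|---|---|
| Exactly normal | 5% | 7% | 5% | 6% |
| Normal, rounded to integers | 5% | 6% | 7% | 8% |
| Skewness 0.2 | 11% | 42% | 50% | 83% |
| Skewness 0.3 | 18% | 72% | 86% | 99% |
| Skewness 0.4 | 27% | 96% | 99% | 100% |
| Skewness 0.5 | 39% | 100% | 100% | 100% |
| t, 20 df | 9% | 28% | 30% | 52% |
| t, 10 df | 25% | 67% | 83% | 98% |
| Bounded 0-144 score, assumed mean 110, SD 18 | 89% | 100% | 100% | 100% |

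At skewness 0.3 the firing rate goes from 18% to 99% through sample size alone.

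**3. Whether a comparison of means is safe there.** Simulation with 788 per arm, 1500 runs per setting, one covariate explaining R² of the outcome variance, and residual skewness 0.5. The skewness of the outcome itself is 0.5·(1 − R²)^1.5, which is 0.46 at R² 0.05 and 0.23 at R² 0.40. This is the region where step 2 shows the gate firing in half to nearly all samples. Under no effect, the rejection rate was 4.3-6.3% across Mann-Whitney, t test and ANCOVA (Monte Carlo standard error √(0.05·0.95/1500) ≈ 0.6 points). With an effect of (1.96 + 0.8416)·√(2/788) = 0.141 SD, chosen to give 80% power unadjusted, the t test had 79-81% power. Leaving the comparison of means therefore gains nothing in this range.

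**4. What adjustment could add.** Same effect of 0.141 SD. Adjustment multiplies the residual variance by (1 − R²).

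| Assumed R² | Mann-Whitney | t test | Adjusted linear model |
|---|---|---|---|
| 0.05 | 81% | 80% | 83% |
| 0.10 | 79% | 80% | 84% |
| 0.20 | 78% | 79% | 88% |
| 0.30 | 80% | 81% | 92% |
| 0.40 | 77% | 79% | 95% |

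Check at R² 0.20: 2.8016/√0.80 = 3.132, and 3.132 − 1.96 = 1.17, which corresponds to about 88% power, as simulated.

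**5. Side by side.** The primary analysis carries centre, gender and super-obesity, and section 16a promises that imbalance will be taken into account. One of the two named fallbacks for the continuous outcomes cannot do this.

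**The case against.** The strongest defence is that this is a condensed article, the analysis plan is not shown, and covariates and reporting format for secondary outcomes normally belong there. That stands as far as it goes: the lack of a named adjusted model is not a finding in itself. But the gate is written into the protocol, and a plan that follows the protocol inherits it.

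Several stronger readings are tempting, and the document does not support them.

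- *Everything ends in an unadjusted Mann-Whitney test.* The sentence also offers a transformation, and a transformed outcome can enter a model with every covariate.
- *The gate nearly always fires.* That depends on an unstated shape. It is true from skewness of about 0.3-0.4, but the rate is only 5-8% for normal or rounded-normal data.
- *The gate discards covariates.* No adjusted default is stated for continuous outcomes, so nothing is shown to be removed. One branch simply cannot use them.
- *The result will be a bare p-value.* The protocol is silent on estimates. A Hodges-Lehmann shift or a mean difference with a CI could accompany a rank test.
- *Adjustment is sure to give a large gain.* %TWL is already divided by initial weight and %EWL by excess weight, so a strong correlation with baseline weight cannot be presumed. GIQLI has no baseline score. At R² 0.05 the gain is small.
- *False-positive risk is inflated.* Each test kept its size in simulation. The free choice between fallbacks was not simulated; it is a matter of prespecification.

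**Conclusion.** The point holds in limited form. The protocol lets a 5% normality test on the outcome data choose the method for %TWL, %EWL and GIQLI, and leaves the choice after a rejection open. At about 788 per arm the test rejects in 50-83% of samples at skewness 0.2 and 86-99% at 0.3, where a comparison of means keeps its size and power. The consequence is possible loss of precision and interpretability, and a method that may change between visits, for secondary outcomes that include the key one. Neither type I error nor the primary analysis is affected.

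The firing rates rest on assumed shapes and the power figures on assumed R² and residual skewness, since the protocol gives none of these. The case for change does not depend on a particular value: the replacement loses nothing in the settings examined and delivers the estimate that the stated aim needs. It is an improvement that should be made, not a flaw that threatens the trial.

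**What to change.** Delete the Shapiro-Wilk rule and the two fallbacks. In their place:

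1. Prespecify one linear model for %TWL, %EWL and GIQLI, either ANCOVA at each visit or a mixed model over months 3 to 24 with arm, visit and arm-by-visit terms.
2. Adjust for centre, gender and super-obesity. Add baseline weight or BMI for the two weight outcomes only.
3. Report the adjusted mean difference at each visit with a 95% CI, using robust standard errors, in percentage points or GIQLI points.
4. Keep a rank test as a sensitivity analysis only.

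All covariates are already recorded. The cost is a change of wording in the protocol and the analysis plan, best made before outcome data by arm are examined. No new data or patients are needed.
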